## Abstract

**Background:**

Social participation is challenging for people with visual impairments. As a result, on average, social networks are smaller, romantic relationships formed later, educational achievements lower, and career prospects limited. Adolescents on their way towards achieving these goals may benefit from the knowledge and experience of adults who have overcome similar difficulties. Therefore, a mentoring intervention, called Mentor Support, will be set up and studied in which adolescents with visual impairments are matched with successfully social participating adults with and without visual impairments. The main objective of this study is to evaluate the effectiveness of Mentor Support. Secondary aims are to distinguish the importance of the disability-specific experience of mentors, predictors of success, and mediating factors.

**Methods/design:**

The effect of Mentor Support will be tested in a randomized clinical trial, using pre-test one week before starting, post-test after 12 months, and follow-up after 18 months. Participants will be referred to one of the experimental groups or the control group, and this randomization will be stratified according to country region. Three groups are included in the trial: 40 participants will receive Mentor Support by mentors with a visual impairment in combination with care-as-usual, 40 participants will receive Mentor Support by mentors without visual impairments in combination with care-as-usual, and 40 participants will receive care-as-usual only. Mentor Support consists of 12 face-to-face meetings of the mentee with a mentor with an overall time period of one year. On a weekly basis, dyads have contact via email, the Internet, or telephone. The primary outcome measure is improved social participation within three domains (work/school, leisure activities, and social relationships). Mediator variables are psychosocial functioning and self-determination. Predictors such as demographics and personality are also investigated in order to distinguish the pathways to successful social participation. Intention-to-treat and completer analyses will be conducted.

**Discussion:**

The primary outcomes of this trial regard increased social participation. The study may yield insights to further improve effects of support programs to adolescents with visual impairments.

**Trial registration:**

Netherlands Trial Register NTR4768 (registered 4 September 2014).

## Background

Young people with visual impairments (VI) dream about their futures just like everybody else. However, hopes of meaningful relationships with others, exciting leisure activities, successful school careers, and work career pursuits are often dampened due to the difficulties engendered by their disabilities. These difficulties are not only experienced when trying to engage in the activities necessary for successful participation (for example, communication and mobility), but may also result from negative responses from others as well as weaker self-efficacy. Adolescents may therefore benefit when society, including rehabilitation services, supports them in the making of choices, identification of opportunities, and the elimination of obstacles to realizing their goals in social participation [1].

A Dutch longitudinal study of adolescents with VI showed that they have relatively small social networks, fewer friends than their sighted peers, date less, have later sexual debut, have low social competencies, spend more time at home, have less peer activity, have trouble establishing a stable partner relation, and less frequently start a family or have children at a later age. This implies that successful social participation is challenging for Dutch adolescents with VI. Although most of them have a degree and jobs, they had to surmount more obstacles than their non-disabled peers in order to achieve these goals [2–6]. Another Dutch study paints an even bleaker picture for persons with VI regarding employment [7]. Across Europe, persons with VI report less job satisfaction, fewer opportunities, and lower pay [8]. Moreover, research reviews conclude that all over the world persons with VI have distinct challenges regarding social participation and inclusion as well as very low relative employment rates [9, 10].

Building blocks for social participation have been shown to include strong parental, family, and other (such as teacher) support for the participation, a sense of self-efficacy or self-determination, and opportunities to gradually build up experience and skills by “testing the waters” [11–13]. Examples of such gradual stacking include dating as a preparation for steady relationships [14], and having summer or weekend jobs as a preparation for long-term employment [15]. Research indicates that rehabilitation services are still seeking to improve their support for social participation. For example, structured school-to-work programs do not enhance the chances of success in employment [16]. The experiences as studied by McDonnall et al. [15, 16] are also verified by young adults in the Dutch longitudinal study [5]. An important question is therefore: How can factors associated with successful participation be implemented in support? The availability of specific, structured programs, professional support in Dutch rehabilitation centers, or adapted training has not yet proven to be enough.

Mentoring programs may address this need for support. According to Vygotsky [17], a person becomes more competent in interaction with a more competent person. Therefore, jointly accomplishing tasks may lead to better outcomes. This concept of zone of proximal development is consistent with the idea of mentoring, whereby a mentee benefits from a slightly older and more experienced person. Also, Deci and Ryan [18, 19] argue on the basis of the self-determination theory that relatedness is one of the three psychological needs that supports well-being, creativity, persistence, and performance. Relatedness refers to the desire to feel connected, cared for, and loved by others and is a fundamental aspect of mentoring. When supporting adolescents with VI, it is important not to focus only on their anatomic disabilities, but also on the social and environmental context as described with the model of International Classification of Functioning, Disability and Health (ICF) [20]. Mentors interact with mentees within their personal context and, thus, may be well-positioned to address the needs for support for adolescents with VI.

The positive effects of mentoring have been extensively documented [21–27]. Mentoring leads to greater career outcomes, more satisfaction with career outcomes, and more commitment in careers [23, 26]. It also leads to an improvement of quality of life and a lower chance of risk behavior, and it facilitates emotional, social, and psychological growth [24, 25]. One study in the United States of America (USA) [28] found positive results for mentoring adolescents with VI, aged between 16 and 26 years, targeting one domain of social participation (academic achievement and career success). Other mentoring projects for persons with VI in the USA, such as Career Connect and MentorMatch, target only employment. None of these studies or projects aims to achieve participation in all three domains of social participation (employment/school, leisure activities, and social relationships) [9]. In addition, MentorMatch and Career Connect are designed for all vocational ages, are not protocol-based, or are conducted on-line only. Therefore, based on the current state of the field, there was a need to develop and test a more comprehensive mentoring program in the Netherlands.

For the purposes of this research, a mentoring intervention called Mentor Support will be developed and tested for adolescents with visual impairments (mentees), aged between 15 and 22 years. Mentor Support consists of joint meetings with a mentor in or near the mentee’s own (usually home) environment during an overall time period of one year. By performing activities and through modeling, mentees gather information and possible actions and strategies to improve their social participation. Mentor Support is based on existing mentoring interventions in the USA such as MentorMatch, Career Connect, Big Brother and Big Sister, and Home Start and is adapted to our target group and theoretical framework consisting of the self-determination theory, the model of ICF, and the zone of proximal development of Vygotsky. Also, scientific knowledge from a previous national longitudinal study among the target group has been used to develop the program of Mentor Support [2–6].

### Trial objective

In the present study the effectiveness of Mentor Support, a mentoring intervention for adolescents with VI, will be examined by the use of a randomized controlled trial. Participants in one experimental group will receive the intervention from a mentor with a visual impairment, participants in another experimental group from a mentor who is sighted, while participants in the control group will receive only care-as-usual. The main objective of this study is to improve social participation of adolescents with VI. Potential mediating variables, such as indicators of psychosocial functioning and self-determination, and predictors will be investigated in order to distinguish the pathways to successful social participation.

### Hypotheses

The main hypothesis in this study is:Adolescents who are assigned to Mentor Support will improve their social participation more strongly in comparison with adolescents assigned to care-as-usual only.

The secondary hypotheses in this study are:Adolescents who are assigned to Mentor Support receiving the intervention from a mentor with a visual impairment will improve their social participation as much as adolescents receiving the intervention from a mentor who is sighted.Adolescents who are assigned to Mentor Support will improve their psychosocial functioning and feeling of self-determination.Adolescents who are assigned to Mentor Support and are self-determined or have a high level of psychosocial functioning will improve their social participation more strongly.

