## Methods

### Study design

This study is a superiority randomized controlled trial with multiple arms: two experimental groups and one care-as-usual-only as the control group. Based on equivalence, the two intervention groups receive care-as-usual plus a mentoring intervention called Mentor Support. The difference between these two groups is determined by the VI of the mentors and not by the way Mentor Support is performed. One group receives Mentor Support from a mentor with a visual impairment and one group from a sighted mentor. The effectiveness of this randomized controlled trial will be tested with pre-test, post-test, and follow-up. This study protocol has been approved by the Ethics Committee of the VU University (VCW.1310.010; Netherlands Trial Register NTR4768).

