### Sample size

The total sample size is based on the expected differences in outcome measures between participants assigned to the experimental arm receiving Mentor Support and the care-as-usual-only arm. For testing the significance of the between-subject factor (primary hypothesis) a sample of 120 participants (40 in each condition) is necessary to achieve an adequate power of .85 within a medium effect size (d = .5) between the conditions over time with a significance level of .05. Due to dropout or unexpected organizational aspects the number of participants could drop to as low as 108 to achieve a high power of .80. To answer the research question concerning the influence of potential mediators or predictors on the effectiveness of Mentor Support, several repeated measures within-between interaction analyses will be performed. Based on a significant level of .05 and a power of .85 (*f* = .25), a total sample size of 110 is needed.

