### Data analyses

Most analyses will be conducted using the software program Statistical Package for the Social Sciences (SPSS). The descriptive analyses will be carried out using standard methods. If necessary, outliers will be checked and winsorized before analyzing. Differences in baseline characteristics between both experimental groups and the care-as-usual-only group will be analyzed and results will be controlled for these differences if needed. For analyzing the primary (social participation on three domains), mediation (psychosocial functioning and self-determination), and predictor (demographic factors and personality) outcomes, ANOVA repeated measures or multilevel analyses will be used. The primary outcomes of participants in both experimental groups will be compared separately from the care-as-usual-only group. Pre-test, post-test, and follow-up will show the change in quantity and quality of social participation, psychosocial functioning, and self-determination as compared with the care-as-usual-only group, over time. Feasibility of the Mentor Support intervention will be analyzed using descriptive analyses. General mixture modeling with M-plus [58] will be used to examine the impact of the Mentor Support intervention on subgroups. Analyses and reporting of the results will be done according to the CONSORT Statement guidelines.

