## Discussion

This study aims to improve social participation of adolescents with VI and compares two experimental groups with one care-as-usual-only group. A secondary objective is to distinguish if psychosocial factors and self-determination mediate this process and if the two experimental groups lead to different social participation outcomes. A strength of this study is the added value of the use of two types of mentors to improve social participation. This might give us more insight into the importance of experiential expertise during mentoring, especially during the transition phase from adolescence to young adulthood. This effect is still uncertain and has never been studied before. Also, the lack of studies about the effectiveness of mentoring interventions to improve social participation makes this study unique. Targeting three domains of social participation is another strength of this study. It provides information about the outcome factors of mentoring and the connectedness of these domains within social participation. A fourth strength of this study is the use of several well-known, frequently used, reliable questionnaires which measure a large number of key variables and factors. This provides the opportunity to look at predictors and mediating effects over time and to compare results from this study with other (international) studies. Another strength of this study is that the target group is a less frequently studied group of persons. Most of the studies concerning people with VI examine developmental problems such as language development, locomotion, and academic achievement. But the total construct of social participation is mostly neglected, especially during the transition phase from adolescence to young adulthood. This study may therefore expand knowledge about social participation development. Finally, a strong aspect of this study is the use of the Internet during the intervention, with a specially designed website. This allows information to be spread easily and all participants to be contacted in the same way. This is especially salient because participants in this study live in several (sub) urban locations throughout the Netherlands, and also because adolescents are likely to be extremely comfortable with web-based interactions and information flow.

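### Secondary hypothesis 1 predicts equal improvement with both mentor types, but no analysis stated in the article can support that conclusion

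*Protocol article*

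**What the plan says.** Five places in the protocol article bear on the comparison of mentor types.

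- **Hypotheses:** adolescents with a visually impaired mentor "will improve their social participation as much as adolescents receiving the intervention from a mentor who is sighted". This predicts equality, and no margin is given.
- **Study design:** "This study is a superiority randomized controlled trial with multiple arms". The next sentence begins "Based on equivalence, the two intervention groups receive care-as-usual plus a mentoring intervention called Mentor Support".
- **Sample size:** the calculation rests on Mentor Support against care-as-usual, and "a sample of 120 participants (40 in each condition) is necessary to achieve an adequate power of .85". Nothing is calculated for one mentor type against the other.
- **Data analyses:** for the outcomes, "ANOVA repeated measures or multilevel analyses will be used". The contrasts described set each mentoring group against care-as-usual. No direct mentor-type contrast is written out.
- **Discussion:** part of the secondary objective is to establish "if the two experimental groups lead to different social participation outcomes".

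**The concern.** The same comparison appears as a prediction of equality in the Hypotheses and as a search for a difference in the Discussion. These aims need different evidence. A difference is supported when the interval excludes zero; equality is supported only when the interval is narrow enough to exclude every gap that matters. The design label, the sample size basis and the stated comparisons all serve the first kind of question.

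The mentor-type question is not marginal. The Abstract lists the mentor's disability-specific experience among the secondary aims, and the closing paragraph of the Discussion gives it as the reason for having three conditions. If the trial reports that the two mentor types work equally well, the reader needs to know what evidence licensed that statement. The article supplies no route to it that would be valid.

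**Working it through.** **Inputs from the article.** 40 per arm; the dropout floor is 108 in total, so 36 per arm; d = .5; alpha .05; measurements before the start, at 12 months and at 18 months; 40 mentors, half with a visual impairment, at most two mentees each.

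**Assumptions, not in the article.** Correlation .5 between occasions; equivalence margins of .3 and .5 SD; SD of 1 at each occasion; no clustering unless stated.

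**1. The plan's own figure.** For a between-groups F test in repeated-measures ANOVA, f = d/2 = .25 and lambda = f² × N × m / (1 + (m − 1) × rho). With three groups, m = 3 and rho = .5:

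- N = 120: lambda = .0625 × 120 × 3 / 2 = 11.25, power .851 (stated .85).
- N = 108: lambda = .0625 × 108 × 3 / 2 = 10.125, power .809 (stated .80).

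The stated power therefore reproduces as a three-group overall test. It is not the power of a 40 v 40 contrast, which at d = .5 on one occasion is .60.

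**2. Precision of a 40 v 40 mentor-type contrast.** SE = SD × √(2/40), and the 95% half-width is t × SE. The SD depends on the model:

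- A, one occasion, unadjusted: SD = 1.
- B, one follow-up adjusted for baseline: SD = √(1 − .5²) = .866.
- C, mean of both follow-ups adjusted for baseline: SD = √((1 + .5)/2 − .5²) = √.5 = .707.

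The chance of non-significance comes from the noncentral t distribution. Equivalence power is for two one-sided tests (TOST) at .05 each with a true difference of zero.

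| Model | SE | 95% half-width | Non-significant, true gap .3 | Non-significant, true gap .5 | TOST power, margin .3 | TOST power, margin .5 |
|---|---|---|---|---|---|---|
| A | .224 | .445 | 74% | 40% | 0 | .43 |
| B | .194 | .386 | 67% | 28% | .01 | .64 |
| C | .158 | .315 | 53% | 12% | .19 | .86 |

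With 36 v 36 the half-widths are .470, .407 and .332, and TOST power at the .5 margin is .35, .57 and .81.

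**3. Shared mentors.** With 20 mentors per type and two mentees each, the variance is multiplied by 1 + ICC. The article gives no ICC. For an assumed range of .05 to .20, half-widths grow by √1.05 = 1.02 to √1.20 = 1.10, so model A becomes .46 to .49 and model C .32 to .35.

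**4. Two comparisons with control.** Under model A an estimated difference is significant when it exceeds .445 SD. Estimates of .45 and .89 SD over care-as-usual would both be significant while the mentor types lay .89 − .45 = .44 SD apart. Significance in both comparisons therefore does not show equality.

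**The case against.** The strongest reply has four parts.

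*A non-significant result is nowhere declared to mean equality.* This is correct. A reader might infer that the plan will confirm the hypothesis by a null p-value on 40 v 40, but the article states no such rule and does not write out that contrast. What stands is narrower: the stated comparisons offer no valid route to the hypothesised conclusion.

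*A condensed article may leave a margin or interval rule to the full protocol or analysis plan, and the named models can produce an estimate with an interval.* Both statements are true, and the absence of a margin alone would be no finding. But the hypothesis, the design label, the sample size basis and the Discussion's version of the aim are all stated here, and they do not agree. A later document would have to choose between them.

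*The reference to equivalence in Study design is not an equivalence design.* This is accepted. It most naturally describes what both mentoring arms receive, since the following sentence says that the groups differ by the mentors' impairment and not in how the intervention is performed. The point does not rely on it. The superiority label also fits the main hypothesis, and a superiority trial may carry a secondary hypothesis of another kind, provided its analysis matches.

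*Single-occasion figures are the least favourable case.* This is also accepted. A reader might infer that non-significance is the expected result even with a meaningful gap, or that the trial simply cannot assess equivalence. At .5 SD, the only effect size the article puts forward for a comparison between conditions, a significant result is more likely than not under every model shown. At a .5 SD margin, equivalence power reaches .86 under model C. Both conclusions depend on the gap or margin and the model.

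**Conclusion.** The mismatch is real and should be fixed. The article hypothesises equal improvement with the two mentor types, while its framework, sample size and stated comparisons address superiority over care-as-usual, and its Discussion asks about a difference. Followed as written, nothing in it could support equality.

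The 95% half-width for mentor type against mentor type is about .45 to .32 SD with 40 v 40, before clustering. The chance of missing a true .5 SD gap is 40% to 12%. Equivalence power is about .43 to .86 at a .5 SD margin and at most about .2 at .3 SD. The favourable end of each range needs baseline adjustment, averaging of both follow-ups and the assumed correlation of .5. The margins are assumptions too.

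This concerns one secondary hypothesis. The main hypothesis, the randomization and the sample size for the primary comparison are unaffected, so it does not rank as a defect that must be cured before the trial can be interpreted.

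**What to change.** 1. Reconcile the Hypotheses with the Discussion, so that the mentor-type question is asked in one way.
2. In Data analyses, specify a direct contrast between the two mentor types, reported as the baseline-adjusted difference with its 95% confidence interval and allowing for mentors shared between mentees, for example with a random effect for mentor.
3. State that a non-significant difference will not be read as equality.
4. Conclude equal improvement only if the 90% confidence interval lies wholly inside a margin fixed before the data are analysed. If no margin can be justified, present the comparison as estimation.
5. Note that the sample size was set for Mentor Support against care-as-usual, and that power for equivalence depends on the margin and the model.

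This changes the wording of the hypothesis and adds a short passage on its analysis. Recruitment, arms and measures stay as they are. According to Trial status, recruitment and data collection were still in progress, so the rule could be set before analysis. The cost is a more modest claim about mentor type.
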